### Random allocation of the intervention

The total of 80 enumeration areas in the four municipalities are home to the four main indigenous groups (Fig. 3). If we allocated the intervention at the level of enumeration areas, we would expect a substantial contamination effect within each municipality (mothers from control enumeration areas going to authentic traditional midwives in the intervention enumeration areas) with strong spill-over influence within the same indigenous group served by the intervention midwives; through schools; and through local government or non-governmental organisations (NGOs) taking up the emerging evidence to guide interventions in control enumeration areas. This contamination would reduce the measured difference between control and intervention enumeration areas. To avoid this, the study will centrally randomise the intervention to two of the four municipalities (40 enumeration areas, 20 in each municipality).

**Fig. 3 Fig3:**
[figure not shown]
Flow diagram of the study Safe Birth and Cultural Safety

### Analysis

#### Data entry and security

Independent operators will enter questionnaire responses twice, with verification of discordant entries from the original questionnaires. Researchers will check digitised data for logical errors. We will handle questionnaires from intervention and control sites in exactly the same way, with data technicians unaware of the intervention status of clusters.

#### Principal analysis

With 80 communities allocated evenly between the intervention and control arms, the principal analysis of primary outcomes will follow intention-to-treat principles using a cluster *t*-test (everyone included in each cluster, per allocation). We will report outcomes as absolute event rates among intervention and control groups, risk difference with two-sided 95% confidence intervals (95%CIs) and one-sided 97.5% confidence intervals for the non-inferiority analysis, and relative risk reduction (RRR) with 95%CI [48]. The intracluster correlation coefficient (ICC) will be calculated by dividing the between-cluster variance by the variance within and between clusters. 

*Sensitivity analysis* will focus on the different ethnic groups and their accompanying government health services. It will also examine the four intervention components separately because, although all components are available for all participating midwives, we expect a range of implementation in practice.

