**Fig. 4 Fig4:**
[figure not shown]
Power of the sample in relation to the margin of non-inferiority for maternal mortality and birth complications

For the secondary outcome of improved skilled birth attendance (birth assisted by traditional midwife or physician), the pilot study suggested a rate of 92% in control communities (k-statistic 0.011). Follow-up of 1438 births in each cluster (two clusters per arm) would detect a 6.2% increase in skilled attendance (92.1% to 97.8%) with 80% power at a significance level of 5% (allowing us to set the non-inferiority margin at 15%).

These calculations assume no interaction effects with cluster as unit of primary analysis in unmatched parallel groups and relied on the trial simulator devised by Taylor and Bosch [56].

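### The principal t-test is described on 80 communities although only four municipalities are randomised; run that way, its confidence limits are too narrow unless municipalities do not differ

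*Protocol article*

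**What the plan says.** Under Random allocation of the intervention, the protocol counts its areas ("The total of 80 enumeration areas in the four municipalities are home to the four main indigenous groups") and rejects randomising them: "If we allocated the intervention at the level of enumeration areas, we would expect a substantial contamination effect within each municipality". Instead, "the study will centrally randomise the intervention to two of the four municipalities (40 enumeration areas, 20 in each municipality".

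Under Sample size calculation, the skilled-attendance calculation uses municipalities: "Follow-up of 1438 births in each cluster (two clusters per arm) would detect a 6.2% increase in skilled attendance (92.1% to 97.8". The section closes with "These calculations assume no interaction effects with cluster as unit of primary analysis in unmatched parallel groups". The Discussion also describes the clusters as whole municipalities.

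Under Principal analysis, the unit appears to change: "With 80 communities allocated evenly between the intervention and control arms, the principal analysis of primary outcomes will follow intention-to-treat principles". The method named for this comparison is given in the words "using a cluster *t*-test (everyone included in each cluster, per allocation". The same paragraph promises "one-sided 97.5% confidence intervals for the non-inferiority analysis". It names no municipality-level term, no degrees of freedom and no baseline adjustment. The multilevel regression appears only under Secondary analysis, also without a named municipality level.

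**The concern.** A cluster t-test is valid when its units are those that were randomised, or when no variation lies above the units used. Here the 20 communities of a municipality receive their allocation together. The protocol itself describes what they share: spill-over through midwives, schools and local government, health facilities that serve the whole municipality, and a staff workshop held once per municipality.

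If two municipalities have fewer birth complications for reasons unrelated to the intervention, a test on 80 communities sees 40 apparently independent confirmations of a difference that rests on two. The non-inferiority limit on birth complications is the trial's main statement that supporting midwives does no harm. A limit that is too tight makes a false claim of non-inferiority more likely.

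**Working it through.** **1. Units.** 5752 expected births / 4 = 1438, the births per cluster in the sample size section, so the cluster there is the municipality. 5752 / 80 = 71.9 births per community. A t-test on 80 units has 78 df (two-sided 5% critical value 1.991). On 4 units it has 2 df (4.303), which is 2.16 times larger before the standard error changes.

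**2. The plan's own power figure.** Skilled attendance, 92.1% v 97.8%, two clusters of 1438 per arm, with the undefined k statistic of 0.011 read as an ICC:
- Design effect = 1 + 1437 × 0.011 = 16.81.
- SE = √[(0.921×0.079 + 0.978×0.022) × 16.81 / 2876] = 0.0235.
- 0.057 / 0.0235 = 2.43.
- Normal-quantile power is 78.3% at one-sided 5%, close to the stated 80%, and 68.0% at two-sided 5%.
- On 2 df the same inputs give 48.6% and 28.7%.

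**3. Error of the 80-community test.** Risk p = 57/248 = 0.230 (pilot controls), so p(1−p) = 0.177. Let M be the variance between municipalities and E the variance of a community result within a municipality.
- True variance of the arm difference: M + E/20.
- Variance the 78-df test estimates on average: M/39 + E/20.

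Example with municipality ICC 0.005, community ICC 0.011 and 71.9 births:
- M = 0.005 × 0.177 = 0.000885.
- E = 0.011 × 0.177 + 0.984 × 0.177 / 71.9 = 0.00437.
- True variance 0.001104; estimated 0.000241; SE too small by √4.58 = 2.14.
- Approximate two-sided error: 2 × [1 − Φ(1.991/2.14)] = 35%.

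Simulation with no true effect gives the following (repeat runs agree to about one percentage point):

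| Municipality ICC (assumed) | Two-sided error, 14 births per community | 72 births per community |
|---|---|---|
| 0 | 5% | 5% |
| 0.001 | 8% | 14% |
| 0.0025 | 12% | 24% |
| 0.005 | 18% | 35% |
| 0.011 | 29% | 48% |

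The nominal 2.5% one-sided error, which is also the non-coverage of the non-inferiority limit, is 9–14% (14 births) and 18–24% (72 births) for ICC 0.005 to 0.011. The four-municipality t-test stays at about 5% two-sided throughout. The 14 births per community are an assumed lower value; 72 follows from 5752/80.

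**4. What the 2-df analysis can deliver.** Birth complications, no true difference, one-sided 2.5%, SE = √[2 × 0.177 × design effect / 2876], noncentral t on 2 df:

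| ICC | Design effect | SE | Power, margin 0.15 absolute | Power, margin 0.15 × 0.230 = 0.0345 |
|---|---|---|---|---|
| 0.001 | 2.44 | 0.0173 | 98% | 22% |
| 0.011 | 16.81 | 0.0455 | 44% | 7% |

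At municipality ICC 0.011, 72 births per community and an assumed community ICC of 0 to 0.02, the median 95% half-width is 2.5–3.7 percentage points with 80 units and 16.3–17.0 with four. There are C(4,2) = 6 possible allocations, so a randomisation test cannot give a one-sided p below 1/6.

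**The case against.** The Principal analysis section never states 78 df and never says that a community is the cluster. Elsewhere the word points to the municipality, so the t-test may be meant at that level, with the 80 communities a loose description of 40 areas per arm. That is a fair reading, and it is why the error figures are conditional. It does not remove the defect: the sentence presents communities as the allocated units, which contradicts the allocation section, and a reader following it would analyse 80 units.

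The size is also open. A reader might infer that the limits are far too favourable as a matter of fact. The document does not support that. Its 0.011 is undefined, concerns skilled attendance, and comes from a pilot in one municipality, which cannot estimate variation between municipalities. Read as a municipality-level coefficient of variation, it would give an error of only 5.2–5.7%. The ICC reading comes close to the stated 80%, but only one-sided at 5%, and the simulator used is not visible.

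A reader might also infer that each municipality holds one indigenous group. The protocol says only that the four municipalities together are home to the four groups, and the argument does not need it. Finally, baseline and final surveys are planned; analysing change could cancel part of any stable difference between municipalities. The principal analysis specifies no such adjustment, so this tempers the figures without answering the point.

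**Conclusion.** The contradiction over the unit of analysis is certain and lies in the current text. As the Principal analysis section reads, the test leaves out the level at which the intervention is randomised, and its limits are too narrow whenever municipalities differ for other reasons. How much too narrow is not known: there is no inflation at zero municipality variance, noticeable inflation at an ICC of 0.001, and severe inflation at 0.005 to 0.011. All these ICC values are assumptions. A later multilevel model does not repair the principal test, because it is secondary and names no municipality term.

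Nor do the figures show that a correct analysis must be inconclusive. With an absolute margin and ICC 0.001, power is about 98%. With a relative margin it is low at both ICC values examined. The protocol does not say which kind of margin the 15% is.

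**What to change.** - Define the cluster as the municipality in Principal analysis, consistent with the allocation section, the sample size section and the Discussion, and drop the statement that 80 communities were allocated.
- Make the principal analysis a t-test on four municipality results with 2 df (critical value 4.303 for the two-sided 95% and one-sided 97.5% limits). A mixed model with a municipality random effect above the community and 2 df for the arm effect is an alternative, with the caution that its municipality variance rests on four units.
- Keep the 80-community test as descriptive only.
- Report the six-allocation randomisation distribution.
- Restate the 80% power for a 2-df analysis over a range of municipality ICCs, say whether the 15% margin is absolute or relative, and limit the non-inferiority claim to what the resulting interval supports.

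No new data are needed; the changes are to wording, the model and the power statement. The real cost is much wider intervals and possibly low power. That follows from randomising two municipalities against two, and rewording cannot cure it.

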**Methods:**

The study includes four indigenous populations in the State of Guerrero (*Nahua*, *Na savi*/Mixteco, *Me’phaa*/Tlapaneco and *Nancue ñomndaa*/Amuzgo), covering approximately 8000 households. A parallel-group cluster-randomised controlled trial will compare communities receiving usual care with communities where traditional midwives received support in addition to the usual care. The intervention was defined in collaboration with participants in a 2012 pilot study. Supported midwives will receive a small stipend, a scholarship to train one apprentice, and support from an intercultural broker to deal with Western health personnel; additionally, the health staff in the intervention municipalities will participate in workshops to improve understanding and attitudes towards authentic traditional midwives. A baseline and a final survey will measure changes in birth and pregnancy complications (primary outcomes), and changes in gender violence, access to healthcare, and engagement with traditional cultural activities (secondary outcomes). The project has ethical approval from the participating communities and the Universidad Autónoma de Guerrero.

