### The pilot study

A pilot cluster-RCT tested the feasibility and acceptability of an intervention to support authentic traditional midwives between 2008 and 2012 [27]. The pilot was not powered to determine the effect of the intervention, but it did measure outcomes in the intervention and control group, in order to establish that the intervention was not likely to have an adverse effect on maternal morbidity and mortality.

The pilot study was conducted in Xochistlahuaca municipality with *Nancue ñomndaa* (Amuzgo) communities and included 16 indigenous women clearly considered to be traditional midwives by the communities. These traditional midwives were randomly assigned into two groups, one of which received a co-designed intervention [28].

Each intervention midwife received financial support to pay an apprentice (about US$8 per month); had access to a local birthing centre (purpose-built, rented or loaned); and received logistical support from a male community health worker who could arrange transport for women referred to the local hospital and who could interact with the hospital staff on behalf of the traditional midwives, many of whom could not speak Spanish. Control communities continued receiving usual care, provided mainly by the healthcare centre (*hospital básico comunitario*) located in the municipal capital of Xochistlahuaca and by traditional midwives without external support. An unknown proportion of indigenous women in the rural areas of the municipality did not receive healthcare either from Western health staff or from traditional midwives.

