Component 3. Improving understanding and attitudes of staff in the local government health centres towards traditional midwives. In this component, senior researchers from the *Centro de Investigación de Enfermedades Tropicales* in the *Universidad Autónoma de Guerrero* (CIET) will lead a workshop in each municipality to present evidence about the role of traditional midwives and the importance of intercultural skills for Western medical practice. The workshop participants will be the personnel from two primary healthcare centres and ten rural health posts in the intervention municipalities. The workshops will focus on presenting technical data to the staff and will not include traditional midwives, to avoid potential confrontation during this initial stage. Although we expect changes in the attitudes of the staff in the intervention municipalities, their clinical practice remains independent of the project.

Component 4. Training of intercultural brokers (*técnicos interculturales de salud*). A total of 17 community-appointed people will receive training. Inclusion criteria are: being a member of the relevant ethnic group and having basic understanding of traditional culture and Western health services. Each community will follow their own customs to select the candidates.

The training programme will build on previous experiences from Colombia tailored to local conditions of Guerrero [34], and its content will be organised into three thematic lines: culture, nature and health (Table 1). This triple thematic approach reflects a concept of health promotion that seeks to implement actions with positive impact not only on individual health but also on the cultural and environmental domains. Each thematic line comprises theoretical and practical sessions totalling 280 hours of class in 2 months. The training will take place in Acapulco, under the supervision of CIET and with support from Colombian instructors from the Centre for Intercultural Medical Studies. The project will provide accommodation and food for the trainees in Acapulco.

**Table 1 Tab1:** Content of the course for training intercultural brokers in Guerrero State (May to June 2015)

Content	Thematic line
*Introductory module*	
Western medicine, biomedical model and traditional health	Health
Memory, will, and concepts about medicinal plants	
Traditional concept of heat and cold	
Self-care	
Nature and environment	Nature
Culture and intercultural dialogue	Culture
Traditional knowledge	

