**Fig. 2 Fig2:**
[figure not shown]
Schedule of enrolment, interventions and assessments for the study Safe Birth and Cultural Safety

Control communities receive usual healthcare services. Usual perinatal care for indigenous women in the Montaña region of Guerrero is provided by Western physicians (54.6%), nurses (4.2%) and traditional midwives without external support (20.7%); however, some 20.5% of these women do not have any antenatal care. Among those who received antenatal care, more than 3 out of ten women received less than five antenatal check-ups, the minimum indicated by Mexican standards [37].

In this region, Western physicians (36%), nurses (8%) and traditional midwives without external support (47.9%) provide usual care for childbirth. Some 8.1% of the indigenous women had other or no source of care [37]. Control municipalities have a healthcare centre (*hospital básico comunitario*) in San Luis Acatlán as well as two rural posts (*centro de salud rural* and *unidad de consulta externa*) in Atlixtac. In both cases, healthcare facilities are located in the population centres and provide services for the entire municipality. Women in remote areas need several hours’ walking or travel by gravel road to reach the closest healthcare facility. Regional general hospitals (Ometepec and Tlapa) attend the complicated cases remitted from these communities [38].

The intervention will become obvious to residents in the intervention sites, and some outcomes (particularly social cohesion) could be influenced by knowledge of intervention status. The main outcome indicators (non-inferiority for morbidity and maternal mortality) and other secondary outcomes would be less susceptible to this bias.

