### Outcome measures

For objective (1), the central concern is the added benefit of supporting traditional midwives in a context of non-inferior maternal and neonatal mortality. The limited size of the populations involved hinders mortality estimates and increases reliance on intermediate outcomes: birth problems among survivors of pregnancy in the past year. We will measure maternal mortality and morbidity and neonatal mortality through direct questions in each household.

Secondary outcomes (objective (2)) include (a) reduction of social disruption, indicated by gender violence against pregnant women and (b) improvement in intermediate outcomes towards more engagement of women in their culture of origin. The CASCADA model describes these intermediate outcomes in a results chain based on the theory of planned behaviour, overcoming the well-documented limitations of the Knowledge, Attitude and Practices (KAP) model [39, 40]: *C*onscious knowledge, *A*ttitudes, positive deviation from *S*ubjective norms, intentions to *C*hange behaviour, *A*gency (individual and collective), *D*iscussion/socialisation of possible action and, finally, *A*ction or change of practice [41]. Two randomised trials in Pakistan and Mexico, a cross-sectional study in Southern Africa, and a qualitative analysis of narratives in three Southern African countries have used the CASCADA model [42–46].

In this case, the CASCADA model will reflect conscious knowledge of the traditional midwife, a positive attitude about using her services, a positive deviation from a negative subjective norm about traditional midwifery, intention to change in a future pregnancy, the agency to implement these choices, discussion of the choices with partners and, ultimately, interaction with the supported traditional midwife.

The economic outcome measures (objective (3)) are described below under ‘Economic analysis’.

The study will have two measurement points: a baseline survey administered by trained bilingual indigenous interviewers (February and March 2015) and a follow-up survey using the same procedure and questions about pregnancy experiences and outcomes to women pregnant during the past year (May 2017). The period of inquiry for the final survey is defined to avoid any overlap with the pre-intervention period. Given the extent of the region, logistical constraints mean it is not feasible to have continuous or mid-term data collection.

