### Economic analysis

The economic dimension is not trivial. Intercultural dialogue can lead to new solutions for health promotion based on adequate use of local resources [50]. Evaluation of the work of traditional midwives should recognise that far fewer official resources support their work than support Western-trained birth attendants. Finally, cultural loss and depletion of natural resources around indigenous communities mean that some authentic traditional midwives cannot work at full capacity and in these cases we may need to implement some actions to strengthen traditional health systems or at least take into account this imbalance in the measurement process.

In 2 years, the intervention might change some population-based maternity outcomes, allowing aggregated costs to be compared between intervention and control municipalities. The concern is to quantify the somewhat increased cost of adding the intervention and the much-increased access this affords to indigenous women. A starting point is an assessment of site-specific maternal health services available to indigenous women from a societal perspective, based on (1) the implementation costs of these services and (2) the implementation costs of the Safe Birth and Cultural Safety project. Site visits and in-person interviews with representatives of services and of the project will assess local implementation costs. We will measure costs in Mexican pesos and convert into US$ to allow for international comparison.

From the results of the final survey, we will identify direct benefits in terms of maternal mortality and morbidity indicators, particularly birth complications. Additional benefits we expect to evaluate are (1) change in access/uptake of services and (2) secondary effects like increases in social capital, health literacy, or community planning skills in maternal health services. Finally, we will identify the completeness and timing of implementation to provide a context. We will express the relation between benefits and differences in costs using cost-effectiveness ratios [51].

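### The principal analysis names no baseline term, although the abstract defines the primary outcomes as changes, only four municipalities are randomised, and the pilot site falls in the intervention arm

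*Protocol article*

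**What the plan says.** On the purpose of the surveys, the abstract of the protocol article states: "A baseline and a final survey will measure changes in birth and pregnancy complications (primary outcomes"). Outcome measures sets the timing: "The study will have two measurement points: a baseline survey administered by trained bilingual indigenous interviewers (February and March 2015"), followed in May 2017 by a survey with the same procedure and questions.

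On the test, Principal analysis states that "the principal analysis of primary outcomes will follow intention-to-treat principles using a cluster" t-test, and then: "We will report outcomes as absolute event rates among intervention and control groups, risk difference with two-sided 95% confidence intervals", with a one-sided 97.5% interval for non-inferiority and a relative risk reduction. No baseline value, change score or covariate appears there. The sensitivity analyses concern ethnic groups with their health services, and the intervention components. Secondary analysis adds a multilevel model using group characteristics, without naming baseline. Economic analysis draws on one survey: "From the results of the final survey, we will identify direct benefits in terms of maternal mortality and morbidity indicators".

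On allocation, Random allocation of the intervention assigns two of four municipalities. Design of the study names them: Atlixtac, San Luis Acatlán, Acatepec and Xochistlahuaca. The account of control communities under The intervention places the control facilities "in San Luis Acatlán as well as two rural posts" in Atlixtac. The intervention arm is therefore Acatepec and Xochistlahuaca. On the pilot: "The pilot study was conducted in Xochistlahuaca municipality with" Nancue ñomndaa communities, between 2008 and 2012.

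**The concern.** The abstract describes a change and the analysis section describes a comparison of rates. These are different estimates, and the article does not say which one carries the non-inferiority conclusion.

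The choice matters more here than in most trials. Two against two municipalities allows only six allocations, so a pre-existing difference in complication rates between arms is likely and would pass directly into an unadjusted risk difference. One possible difference has a known location: midwives in part of Xochistlahuaca were supported by the pilot, and birth complications there were reported less often than among pilot controls. Any remainder of that effect would lower the intervention rate only, which favours a non-inferiority finding. The baseline survey could measure such a difference, but the principal analysis does not say that it will be used.

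**Working it through.** The point disputes none of the plan's figures. Two that bear on it reproduce:
- Births per cluster: 5752/4 = 1438, as in Sample size calculation, which confirms sizing on two clusters per arm.
- Pilot odds ratio for birth complications: (9/82)/(57/191) = 0.37, as stated.

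**1. Chance imbalance.** Inputs: complication rate 57/248 = 23.0% (pilot controls); municipality intracluster correlation (ICC) assumed, because the article gives none for this outcome. With two municipalities per arm, the SD of the true baseline difference between arms is sqrt(2 × ICC × p(1−p)/2) = sqrt(ICC × 0.177). For scale, 15% of 23.0% is 3.4 points.

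| Assumed ICC | SD of difference | Chance it exceeds 3.4 points, either direction |
|---|---|---|
| 0.001 | 1.3 points | 1% |
| 0.005 | 3.0 | 25% |
| 0.011 | 4.4 | 43% |
| 0.02 | 6.0 | 56% |

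**2. Pilot carry-over.** Inputs from The pilot study: 9/91 = 9.9% exposed and 57/248 = 23.0% control, a difference of 13.1 points; exposed share of the pilot sample 94/(94+252) = 27%.
- Full persistence in 27% of Xochistlahuaca births: 13.1 × 0.272 = 3.6 points in that municipality.
- Averaged over two equal intervention municipalities: 3.6/2 = 1.8 points.
- With a share of 10% to 50% and persistence of 25% to 100%: from 0.5 × 0.10 × 0.25 × 13.1 = 0.2 to 0.5 × 0.50 × 1 × 13.1 = 3.3 points.
- Against the margin: 1.8/3.4 is about half if 15% is relative to 23.0%; 1.8/15 = 12% if it is absolute.

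**3. Effect on the non-inferiority error.** Suppose the t-test is run on 40 against 40 areas, with 5752/80 = 71.9 births each and an assumed area-level ICC of 0.011. The SE of the difference is sqrt(2 × 0.177 × (1 + 70.9 × 0.011)/71.9/40) = 1.5 points. With the true effect at the margin, a head start of 1, 2 or 3 points raises the nominal 2.5% error to about 10%, 27% or 52%. At ICC 0.005 the figures are 12%, 33% and 63%; at 0.02 they are 8%, 21% and 40%. This holds whether the margin is absolute or relative.

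**4. What a change score does to precision.** With equal variances at both surveys and baseline–final correlation r (not given), the SE is multiplied by sqrt(2(1−r)): 1.18 at r = 0.3, 1.00 at 0.5, 0.77 at 0.7, 0.45 at 0.9.

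**5. Degrees of freedom.** Four municipality-level changes leave 2 df, critical t 4.30. Adding baseline as a covariate instead leaves 1 df, critical t 12.7. Eighty areas treated as independent would give 78 df and 1.99. At ICC 0.011 the municipality-level SE of the final-rate difference is 4.55 points, so the 2-df half-width is 4.30 × 4.55 = 19.6 points. A change score at r = 0.7 brings it to about 15.2 (19.6 × 0.775).

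**The case against.** Principal analysis does not say which survey supplies the rates. A reader might infer that the plan states final rates only, or that it discards the baseline. It states neither; the final-rate reading is supported by the economic section but remains an inference. How baseline enters a model is also often left to a statistical analysis plan. What survives is narrower: the article itself fixes the principal test and effect measures without baseline, and this does not match its abstract.

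A reader might also infer that the arms are visibly unequal, because the workshops involve "the personnel from two primary healthcare centres and ten rural health posts in the intervention municipalities" (12 facilities) while three are described for the control municipalities. The first count is of workshop sites and the second of facilities in population centres. The categories differ and there are no denominators or distances. The counts may not be like for like and do not by themselves show better access. No baseline outcome data are shown either.

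Randomisation makes the unadjusted comparison unbiased on average over allocations. That is true, but it is little comfort with six allocations and one already drawn. The ethnic-group sensitivity analysis may partly isolate the pilot site, and the multilevel model may absorb some group differences. Neither corrects the principal estimate.

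Finally, a change score can mislead: if a pilot effect is present in 2015 and fades by 2017, subtracting baseline works against the intervention. This stands as a limit on the remedy.

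**Conclusion.** The point holds as a mismatch that should be resolved: the abstract describes changes, the principal analysis names no use of baseline, and four randomised units make that omission consequential. The 1.8 points is an illustration. It is not an upper bound, since 94/346 is a share of the pilot's survey sample rather than of Xochistlahuaca births, and persistence from 2012 to 2017 is assumed; 0.2 to 3.3 points is the range under the other assumptions tried. Its weight against the margin depends on whether 15% is relative or absolute, which the article leaves open. The imbalance figures depend on assumed ICCs, and at 0.001 the problem is small. Nor should a reader infer that baseline adjustment makes inference from four municipalities sound. Principal analysis speaks of 80 communities while randomisation and the skilled-attendance sample size use four clusters, and that has to be settled together with this point.

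**What to change.** Reconcile the abstract with Principal analysis by naming one baseline-adjusted principal estimate: the difference between arms in change from baseline in municipality-level rates, tested on 2 df to match the randomised unit. Report the unadjusted final-rate comparison second. Add one sensitivity analysis that leaves out the Xochistlahuaca communities supported in the pilot. State whether the 15% margin is absolute or relative.

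The change is to analysis wording and needs no new data, because the baseline survey is already part of the design. The statistical costs should be stated with it:
- The change score is noisier than the final rate if the baseline–final correlation is below 0.5.
- It works against the intervention if a pilot effect wanes between the surveys.
- Inference on 2 df gives wide intervals. That cost comes from randomising four units, not from using baseline.

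If follow-up data have already been seen, the date of the change should be recorded.
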